## Abstract

**Background:**

Substance use disorders (SUDs) remain a prevalent public health issue characterized by a substantial disease burden and high relapse rates. The aim of this planned project is to investigate the optimal electrode placement and polarity of transcranial direct current stimulation (tDCS) to reduce cognitive deficits and substance craving in individuals with SUDs, thereby contributing to improved treatment outcomes, including longer abstinence periods and reduced substance use after relapse.

**Methods:**

This paper is a study protocol for a planned study. The study will enroll 162 treatment-seeking individuals aged 18 to 65 years who meet the DSM-5 criteria for alcohol use disorder (AUD), including those with other comorbid SUDs. Besides receiving treatment as usual (TAU), study participants will be randomly assigned to one of six groups: anodal stimulation over right dorsolateral prefrontal cortex (DLPFC; Group 1), left DLPFC (Group 2), or lateral occipital cortex (Group 3); sham tDCS (Group 4); computerized inhibition training (Group 5); or TAU only (Group 6). Assessments will be conducted at baseline (T1), across the directly following investigation days (T2-T4), post-intervention (T5), and at four follow-ups (after 4, 8, 12 and 24 weeks) at the Central Institute of Mental Health (Mannheim, Germany) and at the Psychiatric Center Nordbaden (Wiesloch, Germany). The primary outcomes include changes in craving and inhibitory control measured through a neuropsychological task (modified Go/No-Go task), as well as changes in electroencephalogram (EEG) activity during this task, specifically in event-related potentials including the N200 and P300 components. Secondary outcomes include abstinence days and amount of alcohol consumed.

**Discussion:**

Following the completion of this study, findings from this research could inform future therapeutic strategies for SUD, potentially advancing and complementing SUD treatment approaches by integrating tDCS as a potential relapse prevention strategy. Addressing potential challenges such as participant discomfort and high dropout rates through comprehensive support is vital for the success of this study.

**Trial registration:**

Registered at https://clinicaltrials.gov/study/NCT06959342 (Date 26.04.2025).

## Background

According to the World Health Organization, alcohol consumption leads to approximately 2.6 million deaths per year [1]. In 2019, an estimated 400 million people (7% of the population aged 15 and older) were living with an alcohol use disorder (AUD) [1, 2]. In addition, about 39.5 million people were affected by other substance use disorders (SUDs) [2], which account for approximately 9–24 of life years lost [3]. Substance use is equally widespread in the German population, thus mirroring world-wide of observations of consumption and harm. According to the 2018 Epidemiological Survey of Substance Abuse, 71.6% of respondents consumed alcohol in the past 30 days, and the 12-month prevalence of AUD was 5.9% [4]. Among other drugs, cannabis was the most common, with a 12-month prevalence of consumption of 7.1% (use disorder 1.1%), followed by amphetamines (consumption 1.2%; use disorder 0.3%) [4]. Negative consequences substance use affect not only the individual, but also our society with considerable social and economic losses. Just looking at alcohol, the US was confronted with an approximate 249 billion USD loss in 2010 [5].

Consuming a substance again after a prolonged period of abstinence is defined as a relapse in the context of a pre-existing SUD. A serious relapse is one on which the individual returns completely to previous, detrimental behavioral patterns [6]. Importantly, in individuals being treated for e.g. AUD, the approximate relapse rates range between 20–80% [7]. A relapse due to increased substance craving can be triggered by confrontation with stimuli that were previously associated with the substance [8]. Especially during protracted withdrawal, which is defined as the 4–6 weeks following last substance use, craving induced by substance-associated stimuli plays a critical role in influencing the likelihood of relapse [9]. In both regards, inhibitory control over one’s actions is vital to prevent relapse. Robust inhibitory control may help to control the compulsive drive to consume substances [10], as indicated by the sizeable percentage of patients with SUDs maintaining lifetime abstinence [11]. Recently, this observation has been translated into inhibitory control trainings as a means to improve health-related behaviors [12], such as increasing abstinent days in patients with AUD [13].

Beyond a compulsion to consume a substance, SUD chronically progresses. Affected individuals lose control over regulating substance consumption [14, 15]. Later, consumption is motivated mainly by a desire to evade withdrawal symptoms if use were to be ceased [16]. At the neuronal level, the prefrontal cortex mediates healthy executive functioning that shifts to striatal control over drug-taking behavior in the course of voluntary to compulsive drug use [17]. Due to a chronic substance consumption, SUDs lead to neurobiological impairments in regions relevant for executive functions, episodic memory, visuospatial capacities [18], and inhibitory control over the desire to consume [19, 20]. Also, structural abnormalities in the prefrontal cortex of substance-dependent individuals were observed, like reduced grey matter volume and density in the prefrontal cortex [21–23]. These micro- and macro-structural abnormalities translate into an altered recruitment of prefrontal brain regions and less connectivity with the striatum, which leads to impairments in inhibitory control [24–26]. In participants wanting to quit smoking, Berkman et al. [27] observed less activation in the right frontal cortex during a response inhibition task which was associated with more cigarettes smoked. Higher activation, on the other hand, was related to a reduced coupling between craving and cigarettes smoked. The authors concluded that a higher baseline-response inhibition, as seen in the activation of the right frontal cortex, might have a real-life effect on addictive behavior. In AUD, heightened activation in prefrontal regions during a working memory task might be relevant for executive control and can be seen as a resilience factor regarding possible relapse [28].

Within the prefrontal brain regions, the dorsolateral prefrontal cortex (DLPFC) plays a vital role in top-down regulation of substance craving and substance-taking behavior (inhibitory control) [29]. Impaired control over adequate action selection was associated with reduced activity in the DLPFC [30]. Functional imaging studies also suggest a shift of activation from the ventral to the dorsal striatum associated with lower cortical control when viewing alcohol cues [31], which can be reversed through cue-exposure based extinction training [32]. Ongoing studies use neurofeedback to target these abnormal activation patterns (e.g., striatal hyperactivation or prefrontal hypoactivation) [33]. Other approaches to strengthen cortical inhibitory control over limbic reward-driven behavior include approach-avoidance and inhibition trainings [34–36]. In addition, event-related brain potentials (ERP) derived from electroencephalography (EEG) provide valuable biomarkers in the study of executive functions or incentive salience in SUDs [37]. For example, alterations in ERPs such as the fronto-central N200 (a negative going waveform at 200–300 ms) and the central-parietal P300 (a positive going waveform at 300–500 ms) components have been associated with alcohol use and inhibitory control [38] and predicted relapse [39, 40]. In SUD, during different neuropsychological tasks assessing inhibitory control and error processing, this was observed as less pronounced amplitudes for the N200 and P300 components [41].

In sum, SUDs play a major role within the field of mental disorders and is are marked by a chronic course, including loss of inhibitory control over the consumption, increased substance craving, and repeated relapses. Whereas the prefrontal cortex mediates healthy, executive functioning during the controlled consumption of drugs, a shift to a striatal control represents the compulsive drug-taking habit [17]. According to this view, a loss of cognitive control (or in other words, a weakened inhibitory control) hinders behavioral control of impulses triggered by substance craving due to changes in brain structure and functioning are fundamental to the development of addiction.

### Transcranial direct current stimulation as a potential neuroenhancer in SUD

Transcranial direct current stimulation (tDCS) involves the induction of a constant low-amperage electric current applied to the cortex via surface electrodes positioned on the scalp of the subject. It can be used to enhance or suppress cortical plasticity in the human cortex [42]. The electric current flows from the positively charged anode towards the negatively charged cathode. Consequently, cortical excitability is expected to be enhanced under the anode, and decreased under the cathode [43]. The effect of tDCS on a specific region is determined by the polarity of the stimulation, the frequency of stimulation sessions, and density and duration of the current penetrating the skull [44]. Initially applied to the motor cortex [43, 45], tDCS was later used to target other brain regions in healthy individuals to enhance cognitive functions such as executive performance [46] and working memory [47]. Meta-analyses report that higher intensities and/or longer stimulation durations may amplify these effects in healthy individuals as well as those with mental disorders [48–51].

In the purpose of the present study, we assess the neuroenhancing effects of tDCS to improve the treatment of SUD. Specifically, we aim to apply tDCS in order to increase inhibitory control and thus reduce substance craving in SUD patients. When studying SUD, the DLPFC should be addressed, as this region is involved in (a) decision making, inhibitory control, attentional bias and awareness, and (b) cue-induced or spontaneous craving, and further (c) affects the reward circuitry via efferent connections to the nucleus accumbens and ventral tegmental area [17, 27, 52].

Regarding inhibitory control, tDCS can improve Stroop task reaction times when stimulating the left DLPFC in healthy young adults [53], but findings are mixed in populations with impaired inhibitory control such as attention deficit/hyperactivity disorder. Some studies found an improved inhibitory control after a single session of tDCS over the left DLPFC [54, 55], while others did not [56]. No standardized protocol exists for enhancing inhibitory control via DLPFC stimulation and outcomes appear to be influenced by current direction, including in SUD populations. In individuals with cocaine use disorder, both left and right anodal DLPFC stimulation resulted in a reduction of risky behavior [57] in the balloon analog risk task. However, in the game of dice task, the subjects’ performance depended on laterization: right anodal stimulation reduced risky behavior, while left anodal stimulation increased risky behavior [57]. A similar lateralization-dependent pattern has been observed in chronic marijuana users in a decision-making paradigm [15].

Results of functional imaging studies in SUD are in line with previous studies using multiple tDCS sessions with anodal stimulation over the right DLPFC. Placing the anode over the right DLPFC could elevate activation in this area and lead not only to an improved response inhibition in experimental paradigms, but may also improve real-world forms of response inhibition. However, results on tDCS as an add-on treatment in SUD are still mixed or inconclusive [52]. Regarding substance craving, studies on both left and right anodal DLPFC stimulation have yielded mostly promising results so far for alcohol [58–61], methamphetamine [62], and nicotine [63–66]. Most of these studies only used a single tDCS session, but multiple stimulation sessions (e.g. at least five) seem to result in more stable and longer lasting effects, as measured by time to first relapse [44, 59, 61, 63, 67–69]. In contrast to a sham stimulation, anodal stimulation of the right DLPFC on five consecutive days leads to a rapid reduction of craving in individuals with SUDs when comparing craving of the first to the last stimulation day [68]. Klaus et al. [61] were able to report a median survival time (i.e. time to first relapse) four times longer in the active tDCS group receiving anodal stimulation over the right DLPFC compared to sham stimulation. Interestingly, in alcohol and crack use disorder, effects of multiple tDCS sessions with the electrodes placed over the DLPFC (anodal right) were also observed regarding changes in the event-related potential of the P300 amplitudes in response to substance cues [70]. Further, a positive effect of tDCS on electrocortical (P300 but not N200 components) and behavioral (inhibitory control) measures might be long-lasting [71].

Summarizing previous research, tDCS is recommended as a potential treatment for enhancing specific cognitive performances. Results from work on tDCS in SUD imply that improvement of inhibitory control is more likely after anodal stimulation over the right DLPFC. There are promising results for reduced craving after stimulation over both hemispheres, with more long-term effects following anodal stimulation over the right DLPFC, as well. Lastly, multiple stimulation sessions seem to be more effective than a single session.

Building upon these sparse but promising results of tDCS in SUD as an add-on treatment [52], further research should clarify the questions of (1) laterality of DPFC tDCS stimulation, (2) the influence of tDCS on brain metabolism in general, and a comparison to (3) a computerized inhibition training and (4) sham tDCS as well as treatment as usual, on substance craving, inhibitory control, and abstinence.

### Objectives

Previous research has identified impaired inhibitory control and increased substance craving as key features of SUD, with evidence suggesting that tDCS over the DLPFC can improve executive functions and reduce craving in individuals with SUDs [72, 73]. However, the effects of tDCS seem to be hemisphere-dependent and placebo effects may confound these findings [74].

The proposed study aims to investigate inhibitory control in patients with SUD using computer-based neuropsychological assessments before and after administering five tDCS sessions as compared to an inhibition training or TAU alone. TAU will be a qualified detoxification program. Additionally, the effect of tDCS on inhibitory control will be assessed using EEG recordings, with a focus on the N200 and P300 components. Participants with a main diagnosis of AUD, including those with additional SUDs, will be included. We did not limit the sample to one specific SUD, as excluding certain substances would reduce the generalizability of the results and transferability in the clinical routine. Six groups will be compared: three tDCS conditions, one computerized inhibition training, one sham tDCS group, and one group with treatment as usual only. Multiple sham tDCS could already have a direct, neurobiological effect [75]. Hence, we decided to include two active control conditions (stimulation over the visual cortex and an inhibition training) and one sham tDCS condition.

First, anodal stimulation over the right and the left DLPFC will be compared. For this purpose, stimulation will take place over the F3 (left DLPFC) and F4 (right DLPFC) electrode positions according to the EEG 10–20 system to determine whether inhibitory control is indeed hemisphere-sensitive while craving reduction is not. This would constitute an influencing factor that future studies should consider. If stimulating or inhibiting the DLPFC in the ‘wrong’ direction (i.e., anodal left) indeed increases risky behavior, this might lead to distorted results when the outcome measure is, for example, time to first relapse, even though craving might have been reduced by the stimulation (left and right DLPFC: group 1 and group 2).

Second, due to the poor spatial resolution of tDCS (with one anodal and one cathodal electrode), we will include a control group with the anode over O1 (occipital cortex borderline to the cerebellum) and cathode over Cz to account for potential global effects on brain metabolism and task performance (occipital: group 3).

Third, we further include a computerized inhibition training to examine effects of an active, highly frequent contact and behavioral training compared to tDCS (inhibition training; group 5).

Forth, to avoid confounds related to placebo or practice effects in the neuropsychological assessment, participants following the same protocol with either sham tDCS or without receiving any intervention will be included to control for placebo effects of tDCS and the study participation being a ‘treatment’ by itself (sham: group 4, treatment as usual, TAU: group 6).

As we are interested in whether the tDCS add-on has a superior positive impact on treatment outcome, we will follow up participants for 24 weeks to record relapse timing and frequency.

In summary, tDCS is a promising tool as a neuroenhancer and add-on therapy in SUD. It is non-invasive, safe to use, and can be easily and widely applied and does not require well-equipped clinical or research facilities to be of beneficial use. If successfully reducing substance craving and increasing abstinence rates in our study sample, tDCS may be considered universal to all types of SUD, thus greatly advancing treatment options for individuals with SUDs. We aim to investigate the most effective way to simultaneously improve inhibitory control and craving using tDCS. When proven superior to the control conditions (sham tDCS, tDCS over visual cortex and inhibition training), our results may contribute to developing a gold standard for its clinical application.\

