### Hypotheses

#### Primary: effects of tDCS on inhibitory control and substance craving

Anodal tDCS over the right DLPFC as an add-on-therapy improves inhibitory control in SUD in comparison to anodal stimulation over the left DLPFC or occipital cortex, inhibition training, sham stimulation or TAU alone at T5 and T8.Anodal tDCS over the right DLPFC as an add-on-therapy increases fronto-central N200 and central-parietal P300 ERP amplitudes for substances cues and inhibitory control during task-associated EEG measurements at T5 and T8.Anodal tDCS over the right as well as the left DLPFC as an add-on-therapy reduces craving in SUD in comparison to stimulation over the occipital cortex, inhibition training, sham stimulation or TAU alone from T1 to T9.

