### Statistical analyses

The behavioral and EEG results of the inhibitory control paradigm [78] and craving ratings are defined as primary outcome measures. The results of the inhibitory control paradigm will be compared between testing days before (T1) and after fifth (T5) stimulation or training and after a follow-up period of 12 weeks (T8). Craving rates will be compared before and after the first stimulation/training (T1) and across the subsequent stimulation/training sessions (T2-T5), as well as during the follow-up period (T6-T9). Secondary outcomes include duration of abstinence and amount of substance consumed during the follow-up period.

Regarding the EEG data, resampling (to 250 Hz), filtering (70 Hz high- and 0.1 Hz low-pass filter; 50 Hz notch filter), re-referencing to an average reference, manual inspection, independent component analyses, and segmentation (from –200 to 1200 ms) will be conducted. Removed channels due to technical and regular artifacts (e.g., movement artifacts, excessive noise) will be interpolated using neighboring electrodes. ERP components will be scored as mean amplitudes between 200–300 ms and 300–500 ms over fronto-central and central-parietal electrodes for the N200 and P300 components, respectively. All data (EEG, neuropsychological and psychometric data) will be analyzed using t-tests, repeated measures analysis of variance (rmANOVA) and Pearson correlations. The influence of treatment modality (tDCS add-on intervention over various locations versus inhibition training versus standard treatment) on relapse will be tested with a Cox Regression (outcome variable: time until first relapse). Due to the included individuals and the matched-group design, potential influencing factors on primary and secondary endpoints (e.g., type of substance, severity of SUD, number of comorbidities) will be included in the analyses as covariates. In secondary analyses, we will also take a closer look at the potential influence of these factors on treatment response. In this way, it might be possible to identify subgroups that respond particularly well to the treatment (‘treatment responders’) with the goal of precision-targeted treatments for addiction. Statistical analysis will be conducted using SPSS (IBM Corp., Armonk, N.Y., USA).

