## Discussion

Recent meta-analytic evidence shows that tDCS holds promise as a low-risk intervention for reducing substance craving, with right anodal DLPFC placement exerting more pronounced effects on craving reduction [73]. However, the current body of evidence is limited by the lack of direct comparisons between different anodal electrode placements as well as scarce research examining cognitive outcomes and underlying neurobiological mechanisms, which the present study aims to address. Given the central role of craving in relapse [102], integrating tDCS into existing SUD intervention and prevention strategies could provide a valuable tool for relapse prevention.

To ensure the success of the study, it will be critical to address common practical challenges. Participant discomfort, such as fatigue resulting from five consecutive investigation days, as well as high dropout rates frequently encountered in SUD treatment studies [103], will be proactively mitigated through regular check-ins and individualized support throughout the intervention, as needed. Qualified physicians and psychotherapists will be available to respond to any issues that arise to help create a supportive environment.

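### The objective includes finding that craving reduction is not hemisphere-sensitive, but the craving hypothesis has no right-versus-left contrast and the listed difference tests cannot support a no-difference conclusion

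*Protocol article*

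**What the plan says.** All references are to the protocol article.

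- **Objectives.** The first stated purpose of the group structure is laterality: "First, anodal stimulation over the right and the left DLPFC will be compared", in order "to determine whether inhibitory control is indeed hemisphere-sensitive while craving reduction is not". The section adds that future studies should take the answer into account.
- **Hypotheses, Primary, inhibitory control.** Left DLPFC is a named comparator: right anodal stimulation "improves inhibitory control in SUD in comparison to anodal stimulation over the left DLPFC or occipital cortex", and the remaining controls.
- **Hypotheses, Primary, craving.** Both sides stand on the active side of the comparison: "Anodal tDCS over the right as well as the left DLPFC as an add-on-therapy reduces craving in SUD". The comparators named are the four control arms (occipital, training, sham and TAU only), over the period T1 to T9. Right is not set against left.
- **Sample size.** f = 0.15, alpha 5%, power 80%, repeated-measures ANOVA within-between interaction, 25 per group, with 27 per group (162 in total) enrolled.
- **Statistical analyses.** All data "will be analyzed using t-tests, repeated measures analysis of variance (rmANOVA) and Pearson correlations". Craving is rated before and after the first session, at T2–T5 and at T6–T9.
- **Discussion.** The cited meta-analytic evidence favours the right side for craving, "with right anodal DLPFC placement exerting more pronounced effects on craving reduction [73". The Background section on tDCS likewise reports promising craving results for both hemispheres, with longer-lasting effects on the right.

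**The concern.** The laterality objective has two halves of different logical kinds. For inhibitory control it looks for a difference, and the hypotheses contain the matching contrast. For craving it asks whether there is no relevant difference, and the hypotheses contain no right-left contrast at all.

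Two results could be mistaken for an answer on craving:

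- Both DLPFC arms beat the controls. Right could still be clearly better than left.
- A right-left test is non-significant. With about 25 per arm, that can happen when the sides differ.

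The trial is meant to inform electrode placement. A conclusion that either side serves equally well for craving would therefore be used directly, and the protocol's own literature summary makes a right-sided advantage plausible.

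**Working it through.** **1. Reproduce the planned sample size.** Inputs from Sample size: f = 0.15, alpha 0.05, power 0.80, six groups. The number of measurements m and their correlation rho are not stated. For the within-between interaction, lambda = f² × N × m / (1 − rho), with df (k − 1)(m − 1) and (N − k)(m − 1).

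With k = 6, m = 2, rho = 0.5 and N = 150: lambda = 0.0225 × 150 × 2 / 0.5 = 13.5, df 5 and 144, power 80.6%. The smallest total N reaching 80% is 149, that is 25 per group. The stated figure is reproduced. Other values of m at rho = 0.5 do not give it (m = 3 gives 21 per group, m = 5 gives 17, m = 9 or 10 gives 12).

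**2. Turn the planned effect into a right-left gap.** For two groups of 25, lambda = 0.0225 × 50 × 2 / 0.5 = 4.5, so the t noncentrality is √4.5 = 2.121. Setting d × √(25/2) = 2.121 gives d = 0.60. At rho = 0.5 the SD of change equals the SD of one rating, since √(2 × (1 − 0.5)) = 1. The planned effect in two groups is thus a 0.60 SD gap in change.

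**3. Precision and miss rates at 25 per arm, two-sided 5%.** SE = s × √(2/25) = 0.283 s, and half-width = 2.01 × SE. The residual variance s², in units of one rating's variance, is:

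- single change score: 1
- one follow-up rating, baseline-adjusted: 1 − r²
- mean of q ratings, baseline-adjusted: (1 + (q − 1)r)/q − r²

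| Analysis | s² | 95% CI half-width | Miss a 0.60 SD gap | Miss a 0.30 SD gap |
|---|---|---|---|---|
| Single change score | 1 | 0.57 | 45% | 82% |
| Baseline-adjusted, r = 0.5 | 0.75 | 0.49 | 33% | 78% |
| Mean of 4 ratings, r = 0.5 | 0.375 | 0.35 | 8% | 60% |
| Mean of 8 ratings, r = 0.5 | 0.3125 | 0.32 | 4% | 54% |
| Mean of 4 ratings, r = 0.7 | 0.285 | 0.30 | 3% | 51% |

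The averaged rows assume that the gap persists over the ratings averaged.

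**4. Sensitivity of the first row.** f = 0.15 is an omnibus effect, so the pairwise gap depends on the pattern of means. With m = 2 and rho = 0.5, power for right versus left is 55% (0.60 SD), 60% if the gap equals that between the two DLPFC arms and the four controls (0.64 SD), and 80% if one arm alone departs from the other five (0.80 SD). For the two-group gap it is 42% at rho = 0.3 and 77% at rho = 0.7. Over these cases the miss rate runs from about 20% to 58%. Holding f = 0.15 over 9–10 ratings gives a miss rate of 7–9%, but that set-up does not yield 25 per group.

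**5. What a null result leaves open.** If the two sides were truly identical and a single change score were used, simulation shows that about 87% of non-significant results would still have a 95% CI reaching a 0.60 SD gap.

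**6. Chance of supporting a no-difference claim.** If the true difference is zero, the chance that the 95% CI lies within ±M is about 2Φ(M/SE − 1.96) − 1.

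- M = 0.60, single change score: 2Φ(0.60/0.283 − 1.96) − 1, about 13%.
- M = 0.60, mean of 4 ratings at r = 0.5 (SE = 0.173): 2Φ(3.46 − 1.96) − 1, about 87%.
- M = 0.30, the same averaging: 0.30/0.173 = 1.73, which is below 1.96, so essentially 0%.

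**The case against.** The strongest reply has four parts.

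- **The text asks, it does not assert.** A reader might infer that the trial sets out to show equality, or that the craving question cannot be answered. The documents do not support either. The wording is a question, a right-left comparison is announced in Objectives, and the Discussion presents the lack of direct placement comparisons as a gap to be filled. A large difference could be detected and estimated. Only the no-difference conclusion is unsupported.
- **Power is not always poor.** A reader might infer that a non-significant result is the likely one whenever the sides differ. For a gap of planned size that is not so in the set-up that reproduces 25 per group: detection is somewhat more likely than not with a single change score, and likely with averaged ratings. The high miss rates belong to a gap half that size. This stands.
- **Contrasts, intervals and margins often sit in an analysis plan.** None is shown here, and their absence alone would be no finding. But the objective and the craving hypothesis are both stated in this article and do not match. The stated sample size also limits which margins could be met.
- **The misreading is conjecture.** No section says that a null right-left result will be taken as equality. That is correct. The form of the objective invites the reading but does not commit to it. Nor is the cited right-sided evidence a contradiction: mixed evidence is a reason to compare, and no decision rule assumes equality.

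**Conclusion.** The point holds as a mismatch between objective and hypothesis with a consequence for inference. As written, the trial can show that each DLPFC arm differs from the controls on craving, and it may detect a large right-left difference. It has no stated route to concluding that craving reduction is not hemisphere-sensitive.

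How much a null result leaves open depends on the analysis. A single change score barely excludes the planned 0.60 SD gap even when the estimate is close to zero. Averaged, baseline-adjusted ratings exclude it comfortably but still cannot rule out a gap of half that size. These figures rest on m = 2 and rho = 0.5, which are inferred from the reproduced sample size, on 25 analysed per arm, and on reading f = 0.15 as a two-group effect. The logical point needs none of them. It should be corrected before analysis; it does not threaten the rest of the trial.

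**What to change.** 1. **Contrast.** Add a prespecified two-sided right-versus-left contrast for craving, using the repeated ratings with baseline adjustment and reported as an estimate with a 95% CI.
2. **Claim rule.** State that craving will be called not hemisphere-sensitive only if that interval lies inside a margin fixed in advance. Otherwise report laterality for craving as unresolved. The margin needs a substantive justification, and the authors should recognise that one near 0.30 SD is out of reach at this sample size.
3. **Objective.** Reword the laterality aim as estimating the right-left difference for both inhibitory control and craving.

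The cost is wording in the objectives, hypotheses and analysis sections. No new data or participants are needed. The downside is a more cautious claim about craving.
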